### Intervention

#### Dosage of intervention training

Both BCI-MI and Control-MI training will be completed in 12 weeks with a weekly frequency of 3 sessions per week, lasting 45 min. Treatment adherence is set at 12 of the 36 intervention training sessions. We do not expect the BCI-MI and Control-MI interventions to cause adverse effects (non-invasive procedure; no drug-administration; no adverse events [30]) and both intervention deliveries will be under the care of SCI specialized personnel (physiotherapists, neurophysiology technician experts in patient EEG recordings). To monitor any possible deviation from the intervention training protocols (e.g., missing sessions for intervening illness), a report form for each participant will be compiled at each planned training session by the training personnel and it will be part of the CRF (CRF- Training section; details in Data collection and management section). The study interventions are conceived as add-on to the standard rehabilitation care (treatment as usual; TAU), and both groups will receive the same dosage of TAU and add-on training. To ensure comparability between and within group, TAU will be delivered according to an equal intensive regimen for both groups. The intensive regimen includes neuromotor physiotherapy sessions of 40 min each, twice a day, except on Saturdays, when it is once a day, for 6 days a week.

#### BCI-assisted motor imagery training (BCI-MI, experimental intervention)

An all-in-one BCI-supported MI training station (Fig. 2) developed considering the requirements and specific needs of patients with cervical SCI, will allow to practice the kinesthetic MI of hand closing and opening in a closed-loop condition. To further engage patients during the MI training, and to make it more appealing, the BCI station also includes the option of performing the MI of goal-oriented movements. For example, the hand opening or closing will allow the patient to burst soap bubbles, move billiard balls, and turn on/off light bulbs within a virtual environment. Therapists will choose on a session-by-session basis whether to use animation and also which type in order to introduce variation in the training. The type of animation used in each session will be recorded on the specific training CRF.

**Fig. 2 Fig2:**
[figure not shown]
DiSCIoser BCI station. The Brain-Computer Interface training station developed for patients with Spinal Cord Injury to practice the kinaesthetic motor imagery of hand closing and opening in a close-loop condition. The system is equipped with a laptop, a commercial wireless EEG/EMG system and a screen for the ecological feedback to the participant. The ecological feedback is delivered by means of a custom software program that provides for (personalized) visual representation of the participant’s own hands. The screen for the feedback is adjustable in height and tilt to adapt to use in wheelchair or bed. The participant in the photo filled out the photo release consent form

The feedback that participants receive, i.e., their own hand opening or closing in the virtual environment, will be controlled by the BCI control features. They are those relevant, significant frequency/spatial changes of the EEG signals related to the MI task. The control features will be extracted through offline analysis of the MI-related EEG data collected at $${T}_{pre}$$ (see Neurophysiological Assessment).

A semiautomatic, physiologically driven EEG feature selection method, GUIDER algorithm [62], will be used to process EEG data. Briefly, the GUIDER algorithm permits the user to spatially filter EEG data by means of the common average reference filter, divide EEG data into 1 s-length epochs and extract all spectral features (i.e., spectral amplitude at each frequency bin for each channel) in a reasonable range (0-36 Hz) for each epoch using maximum entropy method (16th order model, 2 Hz resolution, no overlap). A priori criteria for the selection of the relevant control features are then applied: i) features are derived from the fronto-central and centroparietal electrodes that are distributed over both hemispheres; ii) they show desynchronization patterns i.e., a decrease in spectral power at EEG frequencies that are typical for the modulation of sensorimotor rhythms induced by the MI tasks. Thus, through BCI training, we aim to reinforce the individual EEG patterns of reactivity that most resembles the physiological activation that is relevant to the movement imagination of both hands. Qualified neurophysiologists will be instructed to use the GUIDER tool and will flag for each single participant the EEG channels over the scalp sensorimotor areas to be included in the analysis. GUIDER will then extract (regression modeling) the optimal subset of predictor variables that best discriminate between the dependent variables (e.g., task *vs* rest) and it will return an external parameter file ready to be loaded on BCI2000 software [63] for the training sessions.

#### Motor imagery training without BCI support (Control-MI, control intervention)

The Control-MI training will be implemented under the same conditions as the experimental intervention (BCI-MI training). Specifically, the station (Fig. 2) will be used to provide participants only with a visual cue of the MI trial duration that is, the visually represented hand stands still with no BCI control. Participants will perform the same MI tasks (opening/closing hand trial, in random order) as in the experimental intervention training.

#### Training sessions

During training sessions, all participants will be seated on a comfortable chair (or on their wheelchair) in a dimly lit room with their hands and forearms resting under the BCI station screen (Fig. 2). Alternatively, if necessary, it will be possible for the patients to perform the session in bed in a semi-sitting position with hands and forearms resting under the BCI station screen.

Participants will be instructed by the therapists to perform the kinesthetic MI of both hands movements either closing or opening in separate runs randomly ordered. Each training session will consist of 4 runs (20 trials each). In the case of BCI-MI training, each trial will consist of constant baseline period of 4 s and MI task period of maximally 10 s in case of unsuccessful trial, whereas for the Control-MI training the trial length is fixed and randomly choose in the range 4-6 s. In both intervention trainings, EEG data will be collected from 16 EEG electrodes, assembled on an electrode cap according to an extension of the 10–20 International System (ground: left mastoid). Electrode positions will cover the bilateral sensorimotor area (FC3, FC1, FCz, FC2, FC4, C3, C1, Cz, C2, C4, CP3, CP1, CPz, CP2, CP4, Pz). For each participant in BCI-MI group the individual significant EEG features (extracted as described in *BCI-assisted motor imagery training)* section will serve as BCI control features. EMG activity will be continuously recorded through surface electrodes placed over the extensor and flexor digitorum muscles of both hands to ensure that no actual movement is performed during training. EEG and EMG data will be digitalized at 250 Hz (LiveAmp, Brain Products GmbH, Germany).

### Statistical analysis

#### Primary analyses

Baseline characteristics will be described by summary statistics for each group (experimental and control intervention). Differences between groups at baseline $${T}_{pre}$$ will be tested to check that the groups do not differ statistically at baseline.

The primary analysis will be performed in per protocol (PP) population on GRASSP somatosensory score changes between $${T}_{pre}$$ and $${T}_{post}$$. The PP will include all randomized participants who will perform (minimum) 12 training sessions. T-test or Wilcoxon Mann–Whitney rank test for independent groups will be used to compare continuous and discrete outcome measures respectively. Statistical significance will be assessed by two-tailed test.

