### Aim and hypotheses

The “DiSCIoser'' study is a randomized controlled trial (RCT) designed to provide evidence for a significant improvement of hand sensorimotor function induced by a BCI-assisted MI training in patients with traumatic SCI.

Based on our previous findings on the efficacy of BCI-supported MI training in patients with stroke [30], we hypothesise that establishing a real-time contingency between the content of MI and an ecological feedback specifically designed to train MI in patients with SCI will boost the effect of MI training in engaging the sensorimotor system, promoting meaningful cortical sensorimotor plasticity and eventually maximizing recovery of hand function.

Accordingly, the aim of the RCT will be to determine whether the BCI-assisted MI (BCI-MI) training, administered by means of a BCI system fully compatible with a clinical setting, is superior to a non-BCI assisted MI (Control-MI) training in improving hand sensorimotor function outcomes in individuals with traumatic cervical SCI admitted to the ward “Centro Spinale” at Fondazione Santa Lucia for their standard rehabilitation care.

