### Sample size

The sample size was calculated on the hypothesis that experimental intervention (BCI-MI training) is superior in improving the primary outcome measure. Based on preliminary findings in the Upper Extremity Motor Scores (UEMS) from the International Standards for Neurological Classification of SCI (ISNCSCI) ASIA Impairment Scale (AIS) [35] in experimental vs control condition, alpha level at 0.05, statistical power at 80%, and one-tailed t-test, 15 participants per group (Control-MI and BCI-MI) are needed. The analysis was performed using the statistical software STATISTICA 8.0 (Stat Soft. Inc. 1984–2007, USA) according to the algorithm implemented in the tool Power Analysis/Sample Size Calculation.

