### Assessments

#### Outcome assessments

Outcome measures refer to the assessments that will be conducted both before and after intervention. The evaluation timepoints are:

$${T}_{pre}$$ at randomization, before intervention.

$${T}_{post}$$ at the end of the intervention.

(See the SPIRIT diagram in Table 1 for details).

Trained clinical/research staff neurologists, neuropsychologists, neurophysiologists, therapists, and radiologists will perform the assessments and will be blind to the participant intervention allocation except for recruiting neurologists who are not blinded and do not participate to the assessment. Data will be recorded in an ad hoc Case Report Form (CRF; details in Data collection and management section).

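### The only stated primary analysis of a superiority aim is per protocol, on a set defined by attendance after randomisation

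*Protocol article*

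**What the plan says.** Under Aim and hypotheses, the protocol article sets out to determine whether BCI-MI training "is superior to a non-BCI assisted MI (Control-MI) training in improving hand sensorimotor function outcomes". The Sample size section rests on the same kind of hypothesis, that the "experimental intervention (BCI-MI training) is superior in improving the primary outcome measure".

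Under Primary analyses it fixes the population: "The primary analysis will be performed in per protocol (PP) population on GRASSP somatosensory score changes". The set is defined in the next sentence: "The PP will include all randomized participants who will perform (minimum) 12 training sessions". Dosage of intervention training gives the same threshold: "Treatment adherence is set at 12 of the 36 intervention training sessions". As an example of a deviation to be recorded, that section mentions "missing sessions for intervening illness".

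The article names no intention-to-treat or all-randomised analysis, whether primary, secondary or sensitivity. Secondary analyses adds only the secondary outcomes and subgroups by randomisation stratum. The article does not say whether participants with fewer than 12 sessions are assessed at T_post. Under Outcome assessments, T_post is placed "at the end of the intervention".

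**The concern.** Randomisation makes the two groups comparable as allocated. A set chosen by later attendance keeps that comparability only if attendance is unrelated to outcome, or if selection works in the same way in both arms. The article gives grounds to doubt both conditions.

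- **Prognosis.** Illness, the article's own example of a reason for missing sessions, may also affect sensorimotor recovery.
- **Arm.** The experimental group gets closed-loop feedback with optional goal-oriented animations, and an unsuccessful trial can run to 10 s. The control group sees a hand that does not move, in trials of fixed length (4 to 6 s). The trial is single blind with blinded assessors, and no blinding of participants is described. Engagement, and so attendance, could differ between arms.

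At stake is what the headline result means. A per-protocol difference describes those who kept attending; the stated aim concerns the participants assigned to each training. With 15 per arm, two or three exclusions from one side form a visible share of the group.

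**Working it through.** **Inputs from the article.** 15 per arm; threshold 12/36 = 33% of sessions; two-tailed test. The article gives no expected exclusion rate and no link between attendance and outcome, so both are assumed below and shown as a range.

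**The plan's own figure.** The Sample size section gives "alpha level at 0.05, statistical power at 80%, and one-tailed t-test, 15 participants per group (Control-MI and BCI-MI) are needed", without an effect size or SD, so 15 cannot be reproduced forwards. Solving the noncentral t backwards for 15 per arm, one-sided 0.05 and 80% power gives a standardised difference of about 0.93. This is used only in the last step.

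**Bias model.** There is no true effect. Change scores Y are N(0,1) in both arms. A latent tendency to stay in has correlation ρ with Y, and in one arm the lowest fraction p on that tendency is excluded. The spurious difference, in SD, is

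bias = ρ × φ(z_p) / (1 − p), where z_p is the p-quantile of the standard normal.

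- p = 1/15: φ = 0.129, and 0.129/0.933 = 0.139. Bias is 0.04 at ρ = 0.3 and 0.08 at ρ = 0.6.
- p = 2/15: φ = 0.215, and 0.215/0.867 = 0.248. Bias is 0.07 at ρ = 0.3 and 0.15 at ρ = 0.6.
- p = 3/15: φ = 0.280, and 0.280/0.800 = 0.350. Bias is 0.11 at ρ = 0.3 and 0.21 at ρ = 0.6.

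**Type I error.** Simulated, two-sided t-test at 0.05, loss from one arm only. There were 20,000 trials per case for ρ = 0.3 and 0.6. For ρ = 0.5 there were 40,000, with exactly 1, 2 or 3 participants removed.

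| Expected loss, one arm | ρ = 0.3 | ρ = 0.5 | ρ = 0.6 |
|---|---|---|---|
| 1 of 15 | 4.9% | 5.4% | 5.5% |
| 2 of 15 | 5.3% | 6.1% | 6.8% |
| 3 of 15 | 5.5% | 7.2% | 8.2% |

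Simulation error near 5% with 20,000 trials is √(0.05 × 0.95 / 20,000) = 0.15 percentage points, so 4.9% is not distinguishable from 5%.

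**Comparison cases.** With 7% lost in one arm and 20% in the other at ρ = 0.6, bias is 0.12 SD and type I error 6.1%. With 13% lost in each arm through the same mechanism, bias is nil and type I error 5%. Analysing all randomised participants gives 5.0% to 5.3%.

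**Power, illustration only.** At the implied difference of 0.93, two-sided power is 69% with 15 per arm, 62% with 13 and 59% with 12. The article states no allowance for exclusions and stops randomising at the 30th participant.

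**Timing of T_post.** Twelve sessions at 3 per week can be done in 12/3 = 4 weeks. If the end of the intervention means a person's own last session, someone who attends fully and then stops could be assessed 12 − 4 = 8 weeks before a completer. If it means the end of the 12-week course, there is no gap.

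**The case against.** The strongest reply is that the set will be nearly everyone. The threshold is one third of the sessions, participants are inpatients when recruited and the training is planned for the hospital stay, and sessions can be held in bed. If no one falls below 12 sessions, the two populations coincide. The magnitudes above also rest on assumptions: with weak correlation, a single exclusion or equal loss, the inflation is close to zero. All of this stands. It limits the likely size of the problem, but it does not justify the choice of population, and it means the correction costs little.

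It could also be said that an unseen analysis plan may settle the matter. Such a plan could add an all-randomised analysis, but the article has already named the primary population.

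Four stronger readings are tempting, and the article does not support them.

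- **The bias favours BCI-MI.** Nothing shows which arm would lose participants, or whether they would be poor or good recoverers. Loss of good recoverers reverses the sign.
- **BCI set-up burden drives unequal loss.** Both arms use the same station, and EEG (16 electrodes) and EMG are recorded in both. The arms differ in feedback and trial length. Early discharge, another cause one might suppose, is not mentioned.
- **T_post will differ by 8 weeks.** The dosage section says both trainings are completed in 12 weeks, so week 12 is the natural reading. No text makes early stopping trigger an early T_post. The ambiguity would affect an all-randomised analysis equally.
- **Type I error exceeds 10%.** Removing exactly the 2 or 3 worst outcomes from one arm gives 10.8% or 15.7%, but that requires attendance to track outcome perfectly.

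**Conclusion.** The point holds. For a superiority aim, a per-protocol set based on attendance after randomisation is a poor choice as the only stated primary population. This follows from the text and needs no simulation.

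The size is uncertain. With 1 to 3 of 15 lost from one arm only and a correlation of 0.3 to 0.6, the spurious difference is about 0.04 to 0.21 SD and type I error about 5% to 8%. Loss rates, one-sidedness and correlation are all assumed. Equal loss through the same mechanism gives no bias, and few exclusions may occur. The T_post wording is a secondary ambiguity to close, not a demonstrated discrepancy.

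**What to change.** 1. Under Primary analyses, make all randomised participants, analysed in the group to which they were allocated, the primary population.
2. Keep the set with at least 12 sessions as a supportive analysis, labelled as such.
3. Under Outcome assessments, state that T_post is sought at the planned end of the 12-week period for every participant, whatever the number of sessions attended. This removes the early-assessment reading and supplies the data that item 1 needs.

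No extra participants are needed and neither training changes. If everyone is assessed, the comparison stays at 15 versus 15. The costs are revised wording, follow-up of the few who stop early, and a slight dilution of the estimated effect by participants who attended little.

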#### Primary

Changes from pre- $$({T}_{pre})$$ to post- $$({T}_{post})$$ treatment in GRASSP somatosensory scores of bilateral arms (12 is the maximum score for each side, equal to physiological condition) [32] are the primary outcome measure of the trial. Those changes will be computed assessing the difference between $${T}_{post}$$ and $${T}_{pre}$$ scores, or by computing the effectiveness, defined as the ratio between $${T}_{post}$$-$${T}_{pre}$$ difference and the maximum possible improvement for that specific scale, expressed in percentage.

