#### Secondary analyses

All secondary outcomes will be compared between groups. T-test for independent samples and non-parametric tests will be used for continuous and categorical data, respectively. Further explorative analyses will be carried out on primary and secondary outcomes in subgroups of participants identified by strata used in randomization procedure. The statistical methods adopted for primary and secondary analyses will be used. All analyses will be under the expert supervision of the partner SAP.

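### The stated 80% power is for a one-tailed t-test, but the analysis rule, read naturally, sends the primary score to a two-tailed rank test, whose power is not given

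*Protocol article*

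**What the plan says.** The Sample size section of the protocol article states its conditions as "alpha level at 0.05, statistical power at 80%, and one-tailed t-test, 15 participants per group (Control-MI and BCI-MI) are needed". The input was preliminary UEMS data; neither an effect size nor a standard deviation is printed.

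Under Primary outcome assessments, the endpoint is the change in "GRASSP somatosensory scores of bilateral arms (12 is the maximum score for each side, equal to physiological condition". Two forms of that change are allowed: the point difference, or the difference as a percentage of the maximum possible improvement. Nothing says which one is primary.

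Under Primary analyses the test is chosen by type of measure: "T-test or Wilcoxon Mann–Whitney rank test for independent groups will be used to compare continuous and discrete outcome measures respectively". The next sentence adds: "Statistical significance will be assessed by two-tailed test". The article does not say whether the GRASSP somatosensory change counts as continuous or discrete.

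**The concern.** A score counted in points and capped at 12 per side is naturally read as discrete, so the protocol's own rule leads to the Wilcoxon-Mann-Whitney test, whereas the trial was sized for a t-test. If the percentage form is used instead, its values could be called continuous and the rule would lead to the t-test. The choice of outcome form can thus decide the test.

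The two tests answer different questions. The t-test compares mean change; the rank test compares how participants are ordered. Their power can differ, and by how much depends on the distribution of change, in particular on how many participants in each arm do not change at all. At stake is whether the stated 80% describes the planned analysis.

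**Working it through.** **Inputs.** From Sample size: 15 per group, alpha 0.05, 80% power, one-tailed t-test. From Primary analyses: two-tailed testing, and a rank test for discrete measures. Assumed: the effect size, because none is given.

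**1. The effect implied by the plan's own figure.** For a two-sample t-test with n per group, the noncentrality is d·√(n/2) on 2n − 2 degrees of freedom. With n = 15, a one-tailed critical value of 1.701 (28 df) and 80% power, d = 0.931, since 0.931 × √7.5 = 2.549. This is back-solved from the stated sample size and does not confirm it.

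**2. Same effect, two-tailed t-test.** The critical value becomes 2.048 and power is 69.2%. The one-tailed/two-tailed conflict alone costs 80 − 69 = about 11 points, before the type of test is considered.

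**3. Same effect, rank test, simulated.** The statistic is z = (U − n²/2)/√v, with v = (n²/12)·[(N + 1) − Σ(t³ − t)/(N(N − 1))], where N = 30 and t are the sizes of the tied groups. The t-test was run on the same simulated data.

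| Shape of change, 15 per arm | t, one-tailed | rank, one-tailed | t, two-tailed | rank, two-tailed |
|---|---|---|---|---|
| Normal, d = 0.93 | 80% | 77–78% | 69% | 65–67% |
| Rounded to integers, SD 3 | 80% | 78% | 69% | 65–67% |

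At equal sidedness the rank test costs about 2 to 4 points. For 80% power it needs about 16 per arm one-tailed. Two-tailed it needs 20 to 21, against 20 for the t-test.

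**4. Participants who do not change.** The documents give no figure for their share, so a range is shown. The standardised difference is held at about 0.9 throughout.

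| Assumed share unchanged | t, two-tailed | rank, two-tailed |
|---|---|---|
| 20% in both arms | 67–68% | 60–68% |
| 30% in both arms | 67–68% | 50–57% |
| 40% in both arms | 67–68% | 38–41% |
| 50% in both arms (one scenario) | 68% | 24% |
| 40% in both arms, others Poisson with mean 2 v 6 (d = 0.90) | 65% | 38–39% |
| 60% control v 20% BCI-MI, others Poisson with mean 3 v 4 | 68–69% | 69–70% |
| 70–90% control v 18–44% BCI-MI, same gain among changers | 67–70% | 76–79% |

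With equal shares in both arms, the rank test falls well behind once 30% or more are unchanged. When treatment turns non-changers into changers, it equals or beats the t-test.

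**The case against.** The strongest reply is that the mismatch costs little. Under the t-test's own model the rank test loses 2 to 4 points, about one participant per arm. That stands.

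A reader might infer that tied values generally cost the rank test a great deal, or that its power here is about 38%. The documents do not support either. The low figure needs the same large share of non-changers in both arms, meaning that treatment moves nobody from unchanged to changed, and no section gives such a share. The unequal-share rows show the opposite result. The Poisson gains also ignore the ceiling of the scale. Capping them at 24 minus a uniform baseline (a further assumption) lowers the t-test as well, to about 67% one-tailed and 53% two-tailed, so the t-test figure in that row is not a property of this outcome either.

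It can also be said that a rank test is a sound choice for a bounded point score with 15 per arm, and that a UEMS-based sizing formula should not dictate the analysis. That stands too: the rank test is not an error, and moving to a t-test is a trade-off. Nor does the loose rule badly inflate false positives. Reporting the better of the two tests under the null rejected in 5.6% of simulated trials.

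Finally, the Secondary analyses section divides measures differently: "T-test for independent samples and non-parametric tests will be used for continuous and categorical data, respectively". Which secondary score gets which test is detail commonly left to the analysis plan, so it is not counted here.

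None of this makes the stated 80% the power of the test that the rule selects.

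**Conclusion.** The point holds in a limited form. The sample size belongs to a one-tailed t-test, the rule most naturally selects a two-tailed rank test, and the power of that test is not stated. At d of about 0.93 and a normal or rounded shape, the planned analysis has about 66% power instead of 80%. About 11 of those points come from sidedness, which is a separate issue, and 2 to 4 from the test. Across the assumed shares of unchanged participants, two-tailed rank power runs from 24% to 79%, while the t-test stays at about 65 to 70%. The direction of the difference therefore cannot be known from the documents.

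Everything rests on the back-solved d. Because the sizing used UEMS, 80% is not established for the GRASSP somatosensory score under either test.

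**What to change.** Under Primary outcome assessments and Primary analyses, fix one form of the change score and one primary test before unblinding. Either the rank test, or a t-test or permutation test of the mean difference, would serve; label the other a sensitivity analysis. In Sample size, restate the power for the chosen test, two-tailed, with the assumed effect on the GRASSP somatosensory score and the range over assumed shares of unchanged participants in each arm.

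This changes wording and one calculation. It needs no extra patients or data. The cost is a less favourable stated power.

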### Randomization procedure and methods

The random allocation sequence of participants to experimental (BCI-MI training) or control (Control-MI training) intervention groups will be generated by using Matlab (The MathWorks Inc, Natick, Massachusetts, USA, release 2019a).

The randomization sequence will be stratified by age (2 categories: ≤ 50 years old and > 50 years old) [61] and by GRASSP somatosensory scores (2 categories: ≤ 8 and > 8). A 1:1 allocation ratio will be used. For each stratum, the sequence will include 30 random allocations. The allocation sequence is securely stored at FSL. Randomization of participants will stop after randomization of the 30th participant in the study by summing participants in all strata.

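### The primary test adjusts for neither the baseline score nor age, although randomisation is stratified by both; the cost is precision, not bias, and it depends on a pre-post correlation the article does not give

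*Protocol article*

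**What the plan says.** Under Randomization procedure and methods: "The randomization sequence will be stratified by age" (50 or under, over 50) "and by GRASSP somatosensory scores" (8 or under, over 8). The second factor is the T_pre value of the primary outcome. On how the lists are built, the section says "For each stratum, the sequence will include 30 random allocations". It mentions no blocks.

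Under Primary analyses: "The primary analysis will be performed in per protocol (PP) population on GRASSP somatosensory score changes between" T_pre and T_post. The test is a t-test or a Wilcoxon–Mann–Whitney "rank test for independent groups will be used to compare continuous and discrete outcome measures respectively", two-tailed. Neither a covariate nor a stratified version is named. Baseline differences "will be tested to check that the groups do not differ statistically at baseline", and no action is attached to the result.

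The Primary outcome paragraph allows two forms of the change: the plain difference, "or by computing the effectiveness, defined as the ratio between" that difference and the maximum possible improvement, as a percentage. The scale is capped at 12 per side.

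The strata return only under Secondary analyses: "Further explorative analyses will be carried out on primary and secondary outcomes in subgroups of participants identified by strata used in randomization procedure". These subgroup comparisons rely on the same tests as the main ones.

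**The concern.** The design treats age and the baseline score as important enough to stratify by, and the primary analysis then leaves both out. Subtracting the baseline is not the same as adjusting for it. Unless r is close to 1, change stays negatively correlated with baseline, and the ceiling of 12 per side strengthens this, because someone who starts high has little room to rise. The dependence sits in the residual variance and widens the confidence interval. With 30 participants there is little precision to spare, and both covariates are already collected.

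Two smaller features follow from the same approach. The baseline significance test might be taken as protection against imbalance, which it cannot give at this size. Testing each stratum separately does not address whether the effect differs between strata.

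**Working it through.** **Inputs.** From Sample size: 15 per group, alpha 0.05, 80% power, one-tailed t-test, based on UEMS findings; no effect size or SD is given. From Primary analyses: two-tailed test. Assumed: r (0.5, 0.7 and 0.9 shown), equal SD s at T_pre and T_post, normal data.

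**1. The plan's figure.** It cannot be reproduced independently without an effect size. Solving the noncentral t (28 df) for 80% one-tailed power at 15 per group gives d = 0.93 SD of the analysed change. At that d the noncentrality is 0.93 × √(15/2) = 2.55, and two-tailed power is 69%. The fall from 80% to 69% comes from the change of sidedness, not from the present point; 69% is the reference below.

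**2. What subtraction leaves behind.** Var(change) = 2s²(1 − r). Correlation of change with baseline = −√((1 − r)/2): −0.50, −0.39 and −0.22 at r = 0.5, 0.7 and 0.9.

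**3. Variance ratio, ANCOVA to change.** s²(1 − r²) / [2s²(1 − r)] = (1 + r)/2 = 0.75, 0.85 and 0.95.

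**4. Closed-form power with 26 df (baseline and age in the model).** Noncentrality 2.55/√0.75 = 2.94, 2.55/√0.85 = 2.77 and 2.55/√0.95 = 2.62, giving 81%, 76% and 71%. These are upper figures when age is not prognostic, because they leave out the variance cost of chance covariate imbalance when two coefficients are estimated from 30 people.

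**5. Simulation of the actual model.** N = 30, normal outcomes, T_post on group, T_pre and age, two-tailed 5%, 8,000 to 20,000 trials per setting, age not prognostic:

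| Allocation | Test | r = 0.5 | r = 0.7 | r = 0.9 |
|---|---|---|---|---|
| Not blocked | change t-test | 69% | 69% | 69% |
| Not blocked | ANCOVA | 77–78% | 73% | 67–68% |
| Blocks of 4 in strata | change t-test | 70% | 69% | 68% |
| Blocks of 4 in strata | ANCOVA | 80% | 74–75% | 69% |

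If group sizes are also left to chance, both tests lose a little: ANCOVA 76%, 72% and 66% against 68% unadjusted.

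With an assumed age effect of 0.5 SD and blocked strata, the unadjusted test has 67%, 66% and 58% and ANCOVA 79%, 75% and 70%, gains of about 12, 9 and 12 points.

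**6. Type I error.** With blocked strata the unadjusted test rejected in 2.7–4.4% of null trials (nominal 5%); ANCOVA stayed near 5%. Without blocking both were near 5%.

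**7. Baseline test.** An observed imbalance reaches p < 0.05 only beyond 2.048 × √(2/15) = 0.75 SD. Anything smaller passes as no difference.

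**8. Separate subgroup tests (illustration).** Assume an even split in two, 7 or 8 per arm, and the same true d = 0.93 in both halves. Power is 36% or 41% per half, and the chance that exactly one is significant is 2p(1 − p) = 46% or 48%.

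**The case against.** Several points on the other side stand.

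- A reader might infer that the analysis ignores the baseline. It does not: change subtracts it, and the effectiveness ratio is the article's own response to limited headroom. What is missing is adjustment.
- A reader might infer that the standard error is wrong because the design is stratified. The article does not support that. Lists of 30 random allocations per stratum with no stated blocking behave much like simple randomisation, for which the unadjusted standard error is right. With blocking, the test errs on the safe side.
- A reader might infer bias. Leaving out covariates does not bias a randomised comparison. Restricting the primary analysis to the per-protocol population is a separate matter.
- The size is not fixed by the article. The d is back-solved from planning on UEMS, a different scale; r is assumed; equal variances and linearity are doubtful on a capped score; and nothing shows that age is strongly prognostic. Near r = 0.9 without an age effect, adjustment gains nothing and may lose a point or two.
- The rank test may be the one used, since the score is discrete. The figures compare a t-test with a linear model and carry over only approximately.
- The subgroup analyses are labelled exploratory and claim no effect modification. The 46–48% rests on a split that the article does not give.

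The point cannot be set aside as something left to an analysis plan, because the article itself names the primary test.

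**Conclusion.** The concern holds as a loss of efficiency. The primary analysis is an unadjusted two-sample test on change in a trial stratified by age and by the baseline of the same outcome. At d = 0.93 and 15 per arm, two-tailed power of about 69% would become about 77–80% at r = 0.5, 73–75% at r = 0.7 and 67–69% at r = 0.9 with age not prognostic, and the gain would be larger if age matters. The direction is secure for low to moderate r; no single figure is, because r, the SD and the effect size are all absent from the article. The planned test is valid, and conservative if allocation is balanced within strata. The baseline test and the stratum-by-stratum tests are minor, but neither answers the question it appears to ask.

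**What to change.** - **Primary analysis:** ANCOVA of the T_post GRASSP somatosensory total on group, T_pre total and age, reported as an adjusted difference with a 95% confidence interval.
- **Sensitivity:** a rank-based analysis (van Elteren or rank ANCOVA) or a proportional-odds model, because the score is discrete and bounded.
- **Secondary scores:** the same form, each with its own T_pre value.
- **Baseline table:** keep the summary statistics and drop the significance test.
- **Strata:** replace separate tests with group-by-stratum interaction estimates and confidence intervals, noting that they will be imprecise with 30 participants.

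The cost is wording and 2 degrees of freedom. No new data are needed, since age and the T_pre score are already required for randomisation. The one downside is a negligible or slightly negative effect on power if r is near 0.9 and age is not prognostic.
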